### Quality control and quality assurance

The Center for K-cospi prepared for an educational session at the beginning of the pilot study for the participating endoscopists to provide them with information to improve their quality of the colonoscopy procedure. Participating physicians were recommended to keep an average withdrawal time of at least 6 min to fully observe lesions and not to perform more than 5 colonoscopies for pilot study per day for quality control. In addition, a manual for the pilot study was developed and distributed to the participating medical institutions to ensure the pilot study procedure complies with the study protocol. The Center for K-cospi will thoroughly evaluate each colonoscopy with the following quality indicators: the quality of the bowel preparation, cecal intubation rate, withdrawal time, and adenoma detection rate. Furthermore, the Center for K-cospi will conduct regular audits for documentation and video recording of randomly sampled colonoscopies to ensure that guidance to enhance colonoscopy quality is being followed. The Monitoring Committee will be provided with a report on the quality analyses.

### Data analysis plan

Colonoscopy performance, including CRC detection rate and stage-shift, will be reported during the whole study period. Participant data will be matched against the national CRC screening program database of the National Health Insurance Service to compare the performance of the colonoscopy with that of the FIT. After completion of our study, we will analyze the long-term effects of colonoscopy screening, such as CRC mortality and incidence reduction, and its cost-effectiveness by linking data with the Korean Central Cancer Registry and death certificate data of the Korean National Statistical Office. In addition, complications related to colonoscopy over the study period, and satisfaction of participants will also be described. Missing values will not be imputed. The Center for K-cospi will conduct all analyses on de-identified data.

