**Methods:**

This study and its protocols have been approved by the Korean Public Institutional Review Board and the National Cancer Center Institutional Review Board. We obtain written informed consent from all participants. The target population is males and females aged 50–74 years living within the pilot sites. A total of 26,640 participants will be recruited for colonoscopy screening. Subjects who have been diagnosed with CRC, who are currently undergoing treatment for CRC, or who have undergone colonoscopy screening within the past 5 years are not allowed to participate. All participants need to complete baseline questionnaires. This pilot study is currently conducted by 104 endoscopists from 57 national cancer screening institutions (42 primary, 10 secondary, and 5 tertiary institutions) located in Goyang-si, Gimpo-si, and Paju-si. The number of endoscopists, medical institutions, and districts participating in the pilot study will be expanded, if necessary. Participating endoscopists at each medical institution perform colonoscopy and report the colonoscopy results to a centralized electronic case report system. We conduct a telephone survey after 7 days and 4 weeks post-colonoscopy to assess for procedure-related complications and satisfaction of the participants. In case of abnormal findings from colonoscopy screening, we track the results from follow-up diagnostic tests. Data from this pilot study will be linked to the diagnostic workup results, the Korean Cancer Registry, and death certificate data for analysis of the performance, long-term effects, and cost-effectiveness of colonoscopy.

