## Background

Colorectal cancer (CRC) was responsible for more than 10% of the global cancer burden in 2018 [1]. It is the third most common cancer in men and the second most common cancer in women worldwide, with more than 730,000 new cases being diagnosed each year [2]. CRC has a high burden of disease in Korea as well as the second most common cancer and the third most common cause of cancer-related deaths in men and women combined [3].

CRC starts as a locally confined polypoid precursor lesion and has a long preclinical stage, with most symptoms presented at an advanced stage. Morbidity and mortality of CRC can be significantly reduced if the disease is diagnosed and treated at an earlier stage [4, 5]. Therefore, screening for CRC before the development of symptoms may be beneficial for improved long-term outcomes. There are several screening modalities for CRC, which include fecal occult blood test (FOBT), sigmoidoscopy, colonoscopy, computed tomography colonography, and stool or blood DNA test. Colonoscopy allows for the detection and removal of early cancer and precancerous adenoma in one-step, and thus, it may have a large effect on decreasing CRC incidence and mortality.

Since 2004 as part of the National Cancer Screening Program (NCSP), the government of the Republic of Korea has been providing annual fecal immunochemical test (FIT) for free to adults aged 50 years and older as the primary modality for detecting CRC. Individuals with a positive FIT result are then referred for either colonoscopy or double-contrast barium enema, which are both provided free-of-charge. However, 68.7% of the patients preferred colonoscopy as the primary method for CRC screening [6]. There has been consistent demand for the introduction of colonoscopy as the primary method for the national CRC screening program. However, colonoscopy is an invasive and expensive procedure. In addition, it entails a risk of complications, requires extensive bowel preparation, and is difficult to learn. Therefore, the benefits and harms of colonoscopy should be carefully evaluated. Currently, we lack population-based clinical trials investigating both the magnitude of effectiveness and the harms of colonoscopy screening for CRC.

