### Sample size calculation

A calculated target sample size of 26,640 participants will be required to detect significant differences in the rates of cancer detection between FIT and colonoscopy. This is based on an estimated cancer detection rate of 1.2 per 1000 screened with FIT and 2.2 per 1000 screened with colonoscopy.

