**Fig. 1 Fig1:**
[figure not shown]
Flow chart of Korean colonoscopy screening pilot study procedure. *CRC* colorectal cancer

**Table 2 Tab2:** Schedule of enrolment, interventions, and assessments

Time point	Study period				
	Enrolment	Pre-treatment	Treatment	1-week follow-up	4-week follow-up
Enrolment					
Eligibility screen	X				
Informed consent	X				
Baseline questionnaire		X			
Interventions					
Bowel preparation		X			
Colonoscopy			X		
Assessments					
Telephone survey				X	X

The participants are asked to visit the medical institution on a scheduled date after their bowel preparation. Polyethylene glycol (PEG) 4L, PEG 2L, and oral sulfate solution are used as standard bowel preparation regimens in the study. All colonoscopies are performed by the participating endoscopists at each participating medical institution with or without sedation, according tothe preference of the participant. The local pathology labs or pathology labs within the participating medical institutions are responsible for tissue examination.

Endoscopists are responsible for follow-up workups or referral of participants for further investigations following their usual referral process, if necessary. Endoscopists need to provide detailed information to the Center for K-cospi on the screening results, results of additional workup, or details of referral if any.

The participants are informed to consult the hospital or visit the nearest emergency room if they experience any uncomfortable symptoms or complications after the colonoscopy procedure. The Center for K-cospi conduct a telephone survey twice—first within 7 days and the next within 4 weeks after colonoscopy—to collect data on any post-colonoscopy complications such as pain, bleeding, and perforations, which could have occurred and the level of satisfaction of the participants with the colonoscopy screening.

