### Data collection and management

The results of individual participants for the baseline questionnaire, colonoscopy, and pathology are stored in an electronic case report form on secure servers, which can be accessed only by authorized staff at the participating medical institutions. Participants areas signed a unique de-identified study ID and no personal information are stored in the electronic database. The centralized electronic case report form allows the Center for K-cospito continuously monitor the number of scheduled appointments, the number of completed screenings, colonoscopy results, and any missing, inadequate, or pending test results. All hard copy material collected at the participating medical institutions are routinely forwarded to the Center for K-cospi and kept in a secure cabinet. This includes the informed consent forms, screening questionnaires, pathology results, and spreadsheets containing personal information.

Data will be stored for a period of 15 years. For further analysis, the data will be linked to hospital medical records where diagnostic tests will be conducted, the cancer registry data of the Korean Central Cancer Registry, and death certificate data of the Korean National Statistical Office based on informed consent and ethical approval. This will be done to monitor the diagnostic workup, subsequent treatment, stage of cancer diagnosis, and CRC incidence and mortality during the 15 years of follow-up.

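### The article names different case-finding sources for the colonoscopy and FIT sides of the primary detection and stage comparison, which could favour colonoscopy and is cheap to harmonise

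*Protocol article*

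**What the plan says.** The primary outcomes are the cancer detection rate and stage shift (Outcome measures). The sample size rests on the FIT-versus-colonoscopy difference in detection, from "an estimated cancer detection rate of 1.2 per 1000 screened with FIT and 2.2 per 1000 screened with colonoscopy" (Sample size calculation).

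**Colonoscopy side.**
- The abstract's Methods state: "In case of abnormal findings from colonoscopy screening, we track the results from follow-up diagnostic tests".
- Screening procedures and follow-up processes adds: "Endoscopists need to provide detailed information to the Center for K-cospi on the screening results, results of additional workup, or details of referral if any".
- Under Data collection and management, the coordinating centre watches for absent or outstanding results. It also plans linkage to the hospital records where diagnostic tests are done, to "the cancer registry data of the Korean Central Cancer Registry, and death certificate data of the Korean National Statistical Office based on informed consent"; approval by an ethics body is also invoked. Stage at diagnosis is among the items to be monitored this way.

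**FIT side.**
- The Data analysis plan says: "Participant data will be matched against the national CRC screening program database of the National Health Insurance Service to compare the performance of the colonoscopy". FIT is the comparator. The Discussion specifies matching on gender and age.
- No tracking of work-up, hospital-record review or registry linkage is described for the FIT records.
- The Background explains that FIT is a two-step process: "Individuals with a positive FIT result are then referred for either colonoscopy or double-contrast barium enema, which are both provided free-of-charge".

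**Role of the registry.** The article is not consistent here. The abstract lists the performance of colonoscopy among the purposes of linkage, and Data collection and management lists stage. The Data analysis plan ties the registry to long-term incidence, mortality and cost-effectiveness after the study is complete.

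**The concern.** A screening colonoscopy sees the lesion at the index test, and the study then pursues whatever is incomplete. A positive FIT finds nothing by itself. The cancer is established later by another test, possibly at another institution. If such a diagnosis does not reach the programme database, a cancer that FIT led to is not counted. A comparable diagnosis in a colonoscopy participant would be pursued through the endoscopist, the coordinating centre and the hospital record.

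This bias is separate from confounding. Matching on age and sex, or applying the study's eligibility criteria to the FIT records, changes who is compared but not how their cancers are found. Stage is exposed in the same way if it comes from hospital or registry records in one group and from the screening record in the other.

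The comparison rests on few events, so modest differences in capture matter. It is also meant to inform whether colonoscopy becomes the primary test of the national programme.

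**Working it through.** **1. The plan's own figure.** Inputs from the Sample size calculation: p1 = 0.0012 (FIT), p2 = 0.0022 (colonoscopy), mean p̄ = 0.0017. Alpha, power and allocation are not given; I assume two-sided 5%, 80% and 1:1, with no dropout.

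n per group = [1.960·√(2p̄(1−p̄)) + 0.842·√(p1(1−p1) + p2(1−p2))]² / (p2−p1)²

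= [1.960 × 0.05826 + 0.842 × 0.05826]² / 0.001² ≈ 26,640 (26,639.6 before rounding up, with unrounded terms).

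The stated figure is reproduced as the size of one group, and nothing is wrong with it. Expected cancers are 26,640 × 0.0012 ≈ 32 for FIT and 26,640 × 0.0022 ≈ 59 for colonoscopy.

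**2. If the planned FIT rate already reflects incomplete capture.** Let c be the assumed fraction of FIT cancers that the database holds, with colonoscopy capture complete. The true FIT rate is 1.2/c, the true ratio is 2.2/(1.2/c), and the artefact in the planned 1.0 per 1000 difference is 1.2/c − 1.2.

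| Assumed c | True FIT rate per 1000 | True ratio (planned 1.83) | Artefact per 1000 |
|---|---|---|---|
| 90% | 1.33 | 1.65 | 0.13 |
| 80% | 1.50 | 1.47 | 0.30 |
| 70% | 1.71 | 1.28 | 0.51 |

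**3. If the two tests truly detect equally.** Take a true rate of 1.7 per 1000 in both groups (the midpoint of 1.2 and 2.2) and n = 26,640 per group. FIT is observed at 1.7c and colonoscopy at 1.7. With d = 1.7(1−c) and SE = √(2m(1−m)/n), where m is the mean of the two observed rates, the chance of a two-sided 5% result is Φ(d/SE − 1.96) + Φ(−d/SE − 1.96).

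| Assumed c | d per 1000 | SE per 1000 | Chance of nominal significance |
|---|---|---|---|
| 100% | 0 | 0.357 | 5% |
| 90% | 0.17 | 0.348 | 8% |
| 80% | 0.34 | 0.339 | 17% |
| 70% | 0.51 | 0.329 | 34% |

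Nearly all of the excess favours colonoscopy. With a common true rate of 2.2 per 1000, the chances of a significant result in favour of colonoscopy (nominal 2.5%) are 8%, 21% and 42%; with 1.2 per 1000 they are 6%, 13% and 26%.

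**4. If colonoscopy capture is also incomplete.** Only the difference in capture matters. With 90% in both groups, d = 0 and the chance returns to 5%. With 90% for colonoscopy and 80% for FIT, the observed rates are 1.53 and 1.36, d = 0.17, SE = 0.329, and the chance is about 8% instead of 17%.

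**The case against.** The strongest reply is that the article does not establish any under-capture. It does not say how the programme database ascertains cancers. The confirmatory colonoscopy or barium enema after a positive FIT is itself free of charge, and nothing suggests that its results are absent from the programme's records. Colonoscopy capture may be incomplete too: it depends on endoscopist reports and usual referral routes, data from people who withdraw are discarded, and missing values are not imputed. A condensed article also commonly leaves case definitions and time windows to the full protocol or the analysis plan.

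Most of this stands, and it limits the point. A reader might infer that FIT cancers come solely from the screening database and that the primary contrast is therefore inflated. The documents do not support that: registry linkage of FIT records is neither stated nor excluded, and the completeness of the database is not given. A reader might also infer that registry cancers count for colonoscopy but not for FIT in the primary rate. The Data analysis plan assigns the registry to long-term outcomes, and only the abstract and the data-management section leave the wider use open. Nor does the mention of informed consent show that linkage is confined to participants, because the same sentence also invokes ethical approval.

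The objection does not remove the core. The article is not silent: it states a source for each side, and they differ. Even without the registry, tracked work-up and hospital records for participants stand against a programme database for FIT. The Discussion offers matching as the answer to non-randomisation, and matching does not address this.

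**Conclusion.** The point holds as a possible bias, not a demonstrated one. The described case-finding is unequal across the primary comparison. If the programme database misses second-step cancers to a greater extent than the study misses its own, the detection and stage contrasts shift towards colonoscopy. Neither the size nor the net direction can be established from the article. The 8%, 17% and 34% figures are conditional on assumed FIT capture of 90%, 80% and 70%, complete colonoscopy capture, equal true rates of 1.7 per 1000 and 26,640 per group; they are not evidence that capture is that low. The sample size is unaffected. I would grade this as an inexpensive improvement worth making before the comparison is analysed, below the level of a must-fix.

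**What to change.** In the Data analysis plan, define the outcome once for both groups:

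- Screen-detected colorectal cancer is a case recorded in the Korean Central Cancer Registry within the same pre-specified window after a positive index test, wherever the work-up took place. Twelve months is one option.
- State what counts as positive for each test. For colonoscopy this needs care: if any polyp qualifies, the trigger is much broader than a positive FIT.
- Use the same histology codes and registry stage in both groups.
- Extend the planned registry linkage to the matched FIT records.
- Report case-report-form counts and programme-database counts as secondary descriptions. This would also show how complete each source is.

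Reconcile the abstract, Data collection and management, and the Data analysis plan on whether registry cancers enter the primary detection rate. If FIT linkage or a common definition already exists in the full protocol, a sentence saying so would suffice.

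The cost is protocol wording, ethics approval for de-identified linkage of FIT records, and some delay from registry lag. No new participants, visits or procedures are needed. The article gives 31 December 2024 as the approximate end of recruitment, which from protocol version 2.5 of November 2020 leaves time to settle this before analysis.

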### Aim

The primary objective of this study is to evaluate the effectiveness of colonoscopy screening for CRC incidence and mortality in the Republic of Korea. The secondary objectives of this study are to evaluate the complications related to colonoscopy screening and to assess the acceptability of colonoscopy for CRC screening.

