### Participant recruitment

Posters and leaflets have been placed in each participating medical institution, main bus and subway stops, and at public health centers within the pilot sites to raise awareness of the pilot study. In addition, the pilot study has been introduced to local newspapers of the pilot sites.

Potential participants are identified from the participating medical institutions during their visits and invited to participate if eligible. In addition, those who express interest in participating in the pilot study to the Center for K-cospia re guided to the nearest participating medical institution after eligibility screening. Table 1 lists the inclusion and exclusion criteria.

**Table 1 Tab1:** Eligibility criteria

Inclusion criteria	Exclusion criteria
Males and females aged 50–74 years	Subjects who have been diagnosed with CRC or are currently undergoing treatment for CRC
Subjects who live within the pilot sites	Subjects underwent colonoscopy screening within the last 5 years

Subjects are allowed to participate in the pilot study only once. Recruitment was initiated in August 2019 and will continue until the planned sample size is reached.

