Currently, there are four on-going large-scale randomized controlled trials that compare colonoscopy with no screening or fecal immunochemical testing for CRC incidence or mortality in 10–15 years [17]. The trials were launched between 2009 and 2014, and the results of these trials will presumably be presented in 10 years. Therefore, findings from the present pilot study regarding the suitability of colonoscopy as the primary method for CRC screening in organized population-based screening programs are necessary to provide critical insights into the future direction of national CRC screening program in the Republic of Korea.

The protocol of this pilot study has some limitations that should be noted. First, we will not randomizing participants into the two study arms. It is difficult to carry out a randomized controlled trial because FIT is provided free-of-charge every year through the Korean NCSP. To overcome this shortcoming in the study design, the participants will be matched according to their gender and age with the data from the Korean NCSP for CRC to compare the performances of FIT and colonoscopy. Second, the generalizability of the study findings will be limited because the participation rate in this pilot study, the characteristics of participants, and the clinical setting of medical institutions may vary depending on regional characteristics. To minimize this limitation, we selected pilot sites that represent the CRC epidemiology of the whole country and have a balanced characteristic of urban and rural areas. In addition, we evenly included first, second, and tertiary hospitals so that the study can be conducted under real-world circumstances.

In summary, the findings of this pilot study will provide critical information regarding the acceptability and feasibility of colonoscopy as the primary modality of the Korean National Cancer Screening Program. They will lead to more effective and efficient screening programs for CRC.

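### CRC mortality is part of the primary objective, but matching on gender and age cannot separate a colonoscopy effect from health selection; non-CRC mortality should be pre-specified as a negative control

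*Protocol article*

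**What the plan says.** The Aim section of the protocol article states: "The primary objective of this study is to evaluate the effectiveness of colonoscopy screening for CRC incidence and mortality". Mortality is thus part of the primary objective, although the primary outcomes listed under Outcome measures are detection rate and stage shift.

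Under Data analysis plan, once the study is complete, "we will analyze the long-term effects of colonoscopy screening, such as CRC mortality and incidence reduction". The deaths come from "death certificate data of the Korean National Statistical Office", and Data collection and management describes linkage to monitor "CRC incidence and mortality during the 15 years of follow-up".

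On how people enter, Participant recruitment says: "Potential participants are identified from the participating medical institutions during their visits and invited to participate if eligible". People who contact the study centre of their own accord are also directed to a participating institution.

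On confounding, the limitations in the Discussion state: "First, we will not randomizing participants into the two study arms". The remedy offered is that "the participants will be matched according to their gender and age with the data from the Korean NCSP for CRC", and the text presents this as the way to *overcome* the shortcoming. The baseline questionnaire (Screening procedures and follow-up processes) collects symptoms, medical and family history, screening history, medication and lifestyle from participants. The article states no use of these variables in the comparison.

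**The concern.** People who agree to bowel preparation and an invasive test may differ in general health, lifestyle and contact with health care from FIT users of the same age and sex. Applying the same eligibility criteria to both groups would not remove that difference. Matching on two variables does not address it either, and the limitations do not mention it.

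A mortality *reduction* needs a comparator, and the only one the article names is FIT users in the national programme. If the CRC mortality ratio is read alone, nothing in the result shows how much of it comes from who volunteered. At stake is the causal reading of a stated primary objective in a study meant to inform national screening policy. The detection-rate comparison, on which the sample size rests, is not the subject of this point.

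**Working it through.** **1. The plan's own figure.** The article gives 26,640 participants for detection rates of 1.2 and 2.2 per 1000. It gives no alpha, power or allocation ratio, so assume two-sided 0.05, 80% power, 1:1. With p1 = 0.0012, p2 = 0.0022 and mean 0.0017:

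n = [1.960·√(2 × 0.0017 × 0.9983) + 0.8416·√(0.0012 × 0.9988 + 0.0022 × 0.9978)]² / 0.001² = (0.1142 + 0.0490)² / 0.000001 ≈ 26,640 per group.

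The figure reproduces exactly as a group size. It concerns detection only, and the article gives no mortality rates. Everything below therefore rests on assumed rates, with 26,640 people in each group and no attrition.

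**2. What selection does to the ratio.** If selection acts multiplicatively, observed ratio = true ratio × selection ratio. With no true effect and a selection ratio of 0.70 to 0.95, the CRC mortality ratio reads 0.70 to 0.95. In the other direction, a true ratio of 0.80 with a selection ratio of 1.25 reads 0.80 × 1.25 = 1.00, and the benefit is hidden.

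**3. Chance of a significantly lower CRC mortality with no true effect** (two-proportion test, two-sided 0.05; nominal 2.5% in this direction):

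| Assumed 15-year CRC death risk | Selection ratio 0.9 | 0.8 | 0.7 |
|---|---|---|---|
| 0.2% | 7.6% | 19% | 39% |
| 0.4% | 11% | 34% | 66% |
| 0.6% | 15% | 47% | 83% |

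Worked cell (0.4%, ratio 0.8): the risks are 0.0040 and 0.0032, the difference is 0.0008 and SE = √(2 × 0.0036 × 0.9964 / 26,640) = 0.000519. Then z = 0.0008/0.000519 − 1.96 = −0.42, which gives a probability of 34%.

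**4. Precision of a non-CRC mortality ratio.** Person-years per group: 26,640 × 15 = 399,600. At an assumed 3 to 8 non-CRC deaths per 1000 per year, that is 1,199 to 3,197 deaths per group. SE(log ratio) = √(2/1,199) = 0.041 to √(2/3,197) = 0.025, so 1.96 × SE is about 8% to 5%. For comparison, a 0.4% CRC death risk gives 26,640 × 0.004 ≈ 107 CRC deaths per group and 1.96 × √(2/107) ≈ 0.27. The control outcome would be known far more precisely than the outcome it checks.

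**5. Power of the non-CRC comparison to reveal a selection difference:**

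| Assumed 15-year non-CRC death risk | Ratio 0.95 | 0.9 | 0.8 |
|---|---|---|---|
| 5% | 27% | 77% | >99.9% |
| 10% | 49% | 98% | >99.9% |
| 15% | 69% | 99.9% | >99.9% |

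A general-health difference of 10% or more would usually show. A 5% difference often would not.

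**The case against.** The strongest reply is that this is a condensed article, and that negative-control outcomes normally belong in the full protocol or SAP, neither of which is shown. That stands: the absence of a negative control is not in itself a fault here. The point rests on what the article does state, namely that matching on gender and age is its answer to non-randomization in a study whose primary objective includes CRC mortality.

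Several stronger readings are tempting, and the text does not support them:

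- A reader might infer that CRC deaths alone will be analysed. The outcome list is introduced by *such as* and is therefore open, and the death-certificate linkage is not restricted to CRC.
- A reader might infer that age- and sex-matched FIT users are the fixed mortality comparator. The matching is stated for comparing the performance of the two tests, and no comparator is given for the long-term outcomes.
- A reader might infer that selection would necessarily favour colonoscopy. FIT users also attend screening by choice. Interest in colonoscopy may reflect symptoms or family history, neither of which is an exclusion, so the bias could run the other way.
- A reader might infer that procedure deaths go uncounted. Safety monitoring tracks serious complications and includes death among its early-termination criteria.

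It is also fair that a non-CRC control has limits. It detects differences in general health, and it would miss selection on CRC-specific risk. Finally, the linkage is described as "death certificate data of the Korean National Statistical Office based on informed consent and ethical approval", which fits participants; death linkage for the comparators is not described. Any CRC mortality comparison needs comparator deaths, however, so the control outcome adds no requirement of its own.

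**Conclusion.** The point holds in a limited form. The article makes CRC mortality part of the primary objective, enrols self-selected people, and offers only gender and age matching against non-randomization. As stated, the plan gives no means of telling a general-health difference from a colonoscopy effect, in either direction.

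The size cannot be fixed from the document. The 8% to 83% range for a spurious significant reduction, and the 77% to 99.9% power to reveal a ratio of 0.9, depend on assumed 15-year risks (0.2% to 0.6% for CRC death, 5% to 15% for other deaths), assumed selection ratios of 0.7 to 0.9, equal groups and no attrition. They show that the problem could matter and that the diagnostic would be informative at the planned size. They do not show that such selection exists.

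**What to change.** In Data analysis plan:

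- Name the comparator for the long-term outcomes.
- Pre-specify non-CRC mortality as a negative-control outcome in both groups, from the same death-certificate linkage needed for CRC deaths, and report its ratio beside the CRC mortality ratio.
- If a calibrated ratio (CRC divided by non-CRC) is wanted, label it a sensitivity analysis. It assumes equal confounding of both causes and would miss selection on symptoms or family history.

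In the limitations, replace *overcome* with a statement that matching on gender and age reduces confounding but does not remove it, and that a CRC mortality difference will be interpreted in light of the non-CRC ratio. A fixed rule forbidding any mortality claim is not needed.

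The cost is wording and a little more analysis, with no linkage beyond what the CRC mortality comparison already requires. The downside for the sponsor is that a claimed mortality benefit may have to be softened. The outcome should be specified before the long-term results are known, because adding it after a favourable CRC result would be less credible.
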